#### Physical and cognitive exercise

A 5-week active control programme was developed ([name], [name] and TD). This contains two elements that roughly match the decentering training for time and cognitive engagement. First, guided physical movement routines will be completed in lieu of mindfulness grounding exercises (Monday–Tuesday). These movements are intended to emulate the physiological nature of grounding exercises but without an internal focus. Participants will watch short videos in which one member of the research team ([name]) illustrates a basic series of body stretches. Accompanying audio provides additional direction and this was recorded using the same voices from the decentering training programme. Each video comprises 15 stretches, with each stretch held for 30 s and a 10 s break between stretches. The physical movements were selected for their ease and accessibility. Care was also taken to select movements that are safe and cater to a range of physical abilities.

Second, gamified versions of standard cognitive tasks will be completed in lieu of the decentering training (Wednesday–Friday). These games are intended to emulate the cognitive effort associated with decentering exercises. Each participant will have a link that allows them to select one of three games, which can be completed on a personal smart phone (for game outlines, see https://osf.io/aw6c5). Games include: (1) a Multi-Target Visual Search Task wherein participants search and respond to specific targets within a broader stimulus array; (2) a Go/NoGo Task wherein a speeded response is made in response to a ‘go’ signal but inhibited in response to a ‘no go’ signal; and (3) a Digit Recall Task wherein participants must recall a sequence on a number pad (ie, a digit-span task). Adherence to the programme will be encouraged by contacting the participants prior to week 1 and at week 3 to discuss their experiences. Engagement will be monitored by reviewing task completion rates and performance measures (response times and accuracy) at the end of the 5 weeks.

### Outcomes

There are two types of outcome measures in this study (see figure 1 for timeline). These include measures of (1) decentering and (2) mental health. We will also examine if there are any far-transfer effects of decentering training by including measures of (3) cognitive performance. Figure 1 provides a schematic overview of the assessment timeline.

**Figure 1 F1:**
[figure not shown]
A schematic overview of the intervention timeline. ADI, Adolescent Decentering Inventory; CAMM, Child and Adolescent Mindfulness Measure; CAS, COVID-19 Anxiety Scale; CERQ, Cognitive Emotion Regulation Questionnaire; CES-D, Center for Epidemiological Studies-Depression Scale; DERS, Difficulties in Emotion Regulation Scale; EQ, Experiences Questionnaire; ESM, experience sampling methods; ESST, Emotional Stop Signal Task; OBT, own-body transformation task; RCADS, Revised Child Anxiety and Depression Scale; SDQ, Strengths and Difficulties Questionnaire; STAXI, State-Trait Anger Expression Inventory-2 Child and Adolescent; WEMWBS, Warwick-Edinburgh Mental Well-being Scale.

#### Decentering outcome measures

The primary training outcome measure is self-rated decentering as measured using the EQ. A secondary decentering outcome measure is the self-rated use of psychological decentering in response to psychological stressors as measured using ESM. These measures have been included to address research questions 1a and 1b, respectively.

##### Experiences questionnaire

This widely-used self-report assessment features 11 items that explore an individual’s tendency to psychologically decenter from difficult subjective experiences in day-to-day life (eg, ‘I can observe unpleasant feelings without being drawn into them’).^8^ Items are answered using a 5-point Likert scale from 1=‘Never’ to 5=‘All the time’). Psychometric properties were found to be satisfactory (Cronbach’s α=0.893; convergent validity r>0.46).^30^ Scores on the EQ are positively associated with other decentering-related constructs like experiential avoidance (a tendency to attempt to evade difficult thoughts and feelings)^30–34^ and cognitive reappraisal (an ability to reconceptualise situations to modify emotional impact).^27 35^ Finally, EQ scores improve over the course of behavioural and cognitive therapies; the magnitude of such change is associated with key outcomes like symptom severity and quality of life.^23 26 27 36 37^ The EQ will be administered at baseline, mid-intervention and post intervention. We expect mean EQ scores will increase in the decentering training group relative to the active control condition.

##### ESM decentering items

All ESM items are described in table 1. Some items relate primarily to the use of decentering skills. Other ESM items relate to secondary mental health outcomes and are described in the next section. However, all ESM items will be administered during each sample point. Two ESM items have been developed to estimate the momentary use of decentering in response to psychological stressors like difficult feelings, memories or thoughts. These are ‘Since the last beep, I was able to distance myself from unpleasant feelings’ and ‘Since the last beep, I was able to distance myself from unpleasant things on my mind’. Items are answered using a 7-point Likert scale ranging from 1=‘Not at all’ to 7=‘Very much’). ESM items will be delivered 4 times daily across a 5-day ESM baseline period and the 5 weeks of training (see figure 1). All ESM items are described in table 1 (see overleaf). We expect momentary reports of decentering to increase over time in the decentering training group relative to the active control condition.

**Table 1 T1:** Experience sampling items

Item	Question	Rating	Purpose	Conditional
*1*	Right now, I feel…	−5=Very negative, 5=Very positive	Affect	Always shown
*2*	I Feel:		Feelings/mood	Always shown
*i*	*Happy*	1=Not at all, 7=Very much	Feelings/mood	Always shown
*ii*	*Relaxed*	1=Not at all, 7=Very much	Feelings/mood	Always shown
*iii*	*Satisfied*	1=Not at all, 7=Very much	Feelings/mood	Always shown
*iv*	*Enthusiastic*	1=Not at all, 7=Very much	Feelings/mood	Always shown
*v*	*Nervous*	1=Not at all, 7=Very much	Feelings/mood	Always shown
*vi*	*Sad*	1=Not at all, 7=Very much	Feelings/mood	Always shown
*vii*	*Irritated*	1=Not at all, 7=Very much	Feelings/mood	Always shown
*viii*	*Stressed*	1=Not at all, 7=Very much	Feelings/mood	Always shown
*3*	Since the last beep, I felt sucked in by negative feelings?	1=Not at all, 7=Very much	ER | Immersion negative feelings	Always shown
*4*	Since the last beep, I was able to distance myself from negative feelings?	1=Not at all, 7=Very much	ER | Distance negative feelings	Always shown
*5*	Since the last beep, I tried to distract myself from negative feelings?	1=Not at all, 7=Very much	ER | Distraction	Always shown
*6*	Since the last beep, I noticed an unpleasant thought or memory?	1=Not at all, 7=Very much	Thoughts/memories onset	Always shown
*7*	Since the last beep, I was upset by an unpleasant thought or memory?	1=Not at all, 7=Very much	Thoughts/memories onset	Always shown
*8*	The unpleasant thing on my mind was about …	Myself, Others, A combination of these, None of these	Content—self/other	Contingent | (if Q6 !=1)
*9*	The unpleasant thing on my mind was about …	Social things, Professional things, A combination of these, None of these	Content—social/non-social	Contingent | (if Q6 !=1)
*10*	The unpleasant thing on my mind was about …	The past, The present, The future, A combination, None of these	Content—past/future	Contingent | (if Q6 !=1)
*12*	Since the last beep, I felt sucked in by unpleasant things on my mind.	1=Not at all, 7=Very much	ER | Immersion in thoughts/memories	Always shown
*13*	Since the last beep, I able to distance myself from unpleasant things on my mind.	1=Not at all, 7=Very much	ER | Distance from thoughts/memories	Always shown
*14*	Since the last beep, I tried to think differently about things so to feel better.	1=Not at all, 7=Very much	ER | Reappraisal	Always shown
*15*	Since the last beep, I tried to distract myself from unpleasant things in my mind.	1=Not at all, 7=Very much	ER | Distract	Always shown
*16*	Since the last beep, I feel I benefited from the daily programme.	1=Not at all, 7=Very much	Usefulness	Always shown
*Branch 1*	Right now, I am …	Indoors, Outdoors	Branch	Contingent | (if Q6==1)
*Branch 2*	Right now, I am …	Alone, With others	Branch	Contingent | (if Q6==1)
*Branch 3*	Since the last beep, I felt social.	1=Not at all, 7=Very much	Branch	Contingent | (if Q6==1)

ER = Emotion Regulation

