### Intervention

#### Decentering training

A 5-week psychological decentering training programme was developed by [name], [name] and TD, based on our previous protocol.^28^ This involves audio-recorded scripts and an accompanying work book that guides participants through four types of decentering techniques; this structure is partly based on a recent taxonomy of self-distancing (a construct closely related to decentering).^29^ The decentering techniques include: (week 1) *spatial distancing* wherein individuals are taught to reimagine negative memories from a physically distant perspective (eg, ‘replay the memory but as if you’re a fly on the wall’); (week 2) *verbal distancing/cognitive defusion* wherein individuals are taught to rephrase negative self-relevant statements in a way that challenges its literal value and influence over affective behaviour (eg, replacing first person pronouns with one’s name); (week 3) *temporal distancing* wherein individuals are taught to reconsider specific worries from a temporally distant future (eg, ‘how would this seem in 5 years?’); and (week 4) *objective distancing* wherein individuals are taught to adopt a third-person perspective towards negative memories (eg, ‘what is the effect of reliving a difficult memory from the perspective of an objective observer?). Week 5 is a revision week, during which participants will be encouraged to practice a different technique from weeks 1 to 4 each day. These techniques were selected since they are directly targeted at how adolescents relate to and observe day-to-day psychological stressors. Specifically, the goal is to teach adolescents concrete ways to generate an objective (or distanced) self-perspective in response to everyday feelings, thoughts and memories that are unpleasant. We assume this training will develop participants’ decentering ability above their baseline levels.

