Each week will involve 5 audio-recorded exercises (10–15 min) that will be made available using common streaming services. One exercise will be posted each weekday, Monday to Friday. The first two exercises (Monday and Tuesday) are brief mindfulness grounding exercises designed to promote open monitoring of psychological experiences. The next three exercises (Wednesday to Friday) are decentering training exercises as described above. Adherence to the programme will be encouraged by directly contacting the participants prior to week 1 and at week 3 to discuss their experiences so far and allow troubleshooting. Participant engagement will be monitored by reviewing the number of completed workbook exercises at the end of the 5 weeks. Participants will also complete daily diaries. These will include five questions about the intervention and its application, such as ‘Did you complete any of the programme exercises today?’ or ‘During the day, were you able to apply the skills you've learned from the exercises?’ (see online supplemental appendix A). A participant’s engagement in the trial will be discontinued if they elect to withdraw their participation or if they experience serious physical/mental health difficulties that necessitate medical or psychological intervention.

10.1136/bmjopen-2021-056864.supp1Supplementary data

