##### ESM emotional reactivity

This study will examine if the lagged effect of the decentering from difficult thoughts, feelings or memories (time=*n*) on later affect (time=*n* + 1) changes across training. One ESM items will capture general affect: ‘Right now I feel…’, answered on a 11-point Likert scale ranging from −5=Very negative to +5=Very positive. Two separate ESM items will capture the self-initiated use of decentering skills in response to negative mental experiences (table 1). These are: ‘Since the last message, I was able to distance myself from [a] a negative feeling *or* [b] unpleasant things on my mind’. Additional ESM items will check for the occurrence of negative mental experiences. These include checks of (a) negative feelings by asking ‘I feel Nervous/Sad/Irritated/Stressed’ and (b) unpleasant cognitive events by asking ‘Since the last beep, I was upset by a thought or memory’. This will be scored on a 7-point Likert scale from 1=Not at all to 7=Very much.

One item will assess the occurrence of unpleasant thoughts: ‘since the last beep, I noticed an unpleasant thought or memory’. This will allow us to control for the presence of unpleasant cognitive events from which participants can decenter. If the participant’s response is anything other than not at all, they will then complete three items to the content of these thought (table 1, items 8–10). If the participant’s response is not at all, they will complete three unrelated ‘branching’ items (table 1, branch items 1–3). This means the same number of item will always be administered.

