#### Consent and data collection

Recruited volunteers will complete an eligibility check during an initial phone call. Volunteers who are eligible will be invited to participate in the study. Written informed consent will be sought after an initial briefing that explains the data collection protocol (see online supplemental appendix B for consent form). This briefing will also include a tutorial on downloading and using the experience sampling app (PsyMate2; www.psymate.eu). Participants will also have the opportunity to ask any questions. To discourage possible contamination, participants will be asked to keep the content of the study confidential from others. Once consent is provided, participants will be given an anonymous trial identification code and added to an encrypted list for allocation. Participants will also receive a URL link to complete baseline measures. Figure 1 illustrates the full schedule for outcome measures. Participants will receive a tutorial on accessing the intervention materials.

10.1136/bmjopen-2021-056864.supp4Supplementary data

Over 5 weeks, participants in both interventions will access and rehearse exercises (Monday–Friday). Decentering training exercises are based on audio files to be delivered via their preferred music/poststreaming services (eg, Spotify/Podcast Addict). The active control exercises are based on YouTube videos posted on a Private Channel. Each day, the PsyMate2 App will prompt participants to complete their daily exercise as well as complete any required ESM items. These will be sent four times per day. A brief survey will also be sent through email each evening to ask whether participants completed their daily exercises, and if so, to ask about their experiences as well as questions on their mood states. At the end of week 5, participants will be asked to complete the online assessment battery. Participants will then complete a debriefing session. During the debriefing session, they will be given the opportunity to provide feedback on their experience of the study, and to ask any questions they may have. They will also be given a list of relevant mental health resources should they feel the need to access them.

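### The ESM decentering items do not exclude the assigned exercise, so in one arm some training-period beeps can report set practice rather than self-initiated decentering

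*Protocol article*

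**What the plan says.** All references are to the protocol article.

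- **Items.** Table 1 items 4 and 13 rate distancing from negative feelings and from unpleasant things on one's mind. The section on ESM decentering items words the second as "Since the last beep, I was able to distance myself from unpleasant things on my mind". Both are shown at every beep, on a 1 to 7 scale.
- **Schedule of beeps.** "ESM items will be delivered 4 times daily across a 5-day ESM baseline period and the 5 weeks of training". The number of ESM days per training week is not stated.
- **Schedule of exercises.** In the section on decentering training: "One exercise will be posted each weekday, Monday to Friday". Monday and Tuesday are mindfulness grounding. "The next three exercises (Wednesday to Friday) are decentering training exercises as described above".
- **Content.** In week 1, for example, "individuals are taught to reimagine negative memories from a physically distant perspective". Later weeks apply distancing to self-statements, worries and memories, and week 5 revises a different technique each day.
- **Control arm.** Stretching on Monday and Tuesday, and gamified cognitive tasks from Wednesday to Friday.
- **Target of the items.** In the section on ESM emotional reactivity: "Two separate ESM items will capture the self-initiated use of decentering skills in response to negative mental experiences".
- **Analysis.** A linear growth model for the effect of condition over the intervention, with unspecified potential confounders as covariates, then a lagged model of decentering at one beep on affect at the next.

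**The concern.** The recall window of items 4 and 13 is everything since the previous beep, and the exercise falls inside one of those windows. In the decentering arm the Wednesday to Friday exercise is the very act that the item rates. A participant who answers truthfully at the next beep may be describing the homework. Controls have no such activity to report, and the five-day ESM baseline comes before any exercise. The extra source of reported distancing therefore starts with training and exists in one arm only.

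This matters because the ESM measure answers research question 1b; the Abstract calls it coprimary and the section on decentering outcome measures calls it secondary. The Introduction justifies ESM as a way to see decentering used in everyday life. An arm difference that partly reflects completed assignments would not show that. No item listed in Table 1 marks an interval that contains an exercise. Item 16 asks about perceived benefit from the programme, not whether an exercise was done.

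**Working it through.** **The plan's own figure.** The article gives no number for the ESM outcome; power rests on the Experiences Questionnaire. That calculation reproduces. An ANCOVA F-test with f = 0.3, alpha 0.05 and N = 90 (df 1 and 87) has power 0.804, and 45 per arm / 0.8 = 56.25, so 57. It is not affected by this point. The 45 completers per arm are used below.

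**Step 1: share of beeps affected.** Inputs: 4 beeps per day, 5 training weeks, 3 distancing exercises and 2 grounding sessions per week. Assumptions: each exercise falls in one interval, and adherence is full.

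| Exercises counted | ESM on weekdays (100 beeps) | ESM on 7 days (140 beeps) |
|---|---|---|
| Distancing only, 3 per week = 15 | 15% | 10.7% |
| Distancing, daily in week 5: 4 × 3 + 5 = 17 | 17% | 12.1% |
| All exercises, 5 per week = 25 | 25% | 17.9% |

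**Step 2: shift in level.** Shift = share × rise in the item within an exercise interval. The documents give no rise, so it is an assumption. For 1 to 2 points on the 1 to 7 scale:

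- distancing only: 0.107 × 1 = 0.11 up to 0.15 × 2 = 0.30 points;
- all exercises: 0.179 × 1 = 0.18 up to 0.25 × 2 = 0.50 points.

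This shift enters both the arm difference in level and the change from baseline. Incomplete adherence scales it down: at 80%, 0.15 × 2 × 0.8 = 0.24.

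**Step 3: does it reach the growth slope?** Let d be a constant shift in all five training weeks, and code the weeks −1 (baseline) and 0 to 4 (training), equally weighted.

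- *Baseline on the time axis:* mean time is 1.5, the squared deviations sum to 17.5, and the deviations of the training weeks sum to 2.5. Slope = d × 2.5/17.5 = d/7. With d = 0.24 this is 0.034 per week; with d = 0.25 × 2 × 0.8 = 0.40 it is 0.057.
- *Training weeks only, constant load:* a constant shift adds nothing to the week-to-week slope.
- *Training weeks only, share rising from 15% to 25% in week 5:* extra shift 0.10 × 2 × 0.8 = 0.16 in the last week; slope = 0.16 × 2/10 = 0.032.

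A simulation with no change in self-initiated use gives the same pattern. Its assumptions are 45 per arm, between-person SD 1.2, within-person SD 1.3, 70% beep response, 80% adherence, slope SD 0.05 to 0.15 per week, and a 2-point rise. With no rise it rejected in about 3% to 7% of runs, as it should at a nominal 5%.

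| Time axis and exercise load | False-positive rate for condition by time |
|---|---|
| Baseline included, 15 to 25 intervals | about 22% to 88% |
| Training only, 25 intervals, constant | about 6% to 7% |
| Training only, 15 intervals | about 8% to 13% |
| Training only, 17 intervals (daily practice in week 5) | about 25% to 44% |

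With baseline included, the simulated slopes were about 0.045 to 0.066 per week. They exceed the hand figure where the exercises sit late in the week or practice rises in week 5.

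**The case against.** Several counter-arguments carry weight.

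- **Direction and size are not in the documents.** An exercise that evokes a bad memory could lower a novice's rating of how well they managed to distance. A reader might infer that the decentering arm will certainly score higher with no real change. The text supports only a likely upward direction of unknown size.
- **The planned test is a slope.** A reader might turn the level shift into a spurious effect size for question 1b. Under a constant load and a training-only time axis, the slope is nearly untouched. This stands, but the article does not fix the time axis.
- **Some separation is possible afterwards.** In weeks 1 to 4 no new distancing exercise is posted on Monday or Tuesday. The evening diary records completion and also asks about applying the skills. It would be wrong to say that practice and spontaneous use can never be told apart. But the diary as described works by day, not by interval, and an exercise posted on one day may be done on another, so the separation is partial.
- **Question 1b does not use the term self-initiated.** True; it asks about decentering in response to negative mental events. The self-initiated label is given in the section on emotional reactivity, but to these same two items.
- **Question 2b.** A reader might infer that emotional reactivity is contaminated as well, because the exercise can also raise the stressor items 6 and 7. The plan is a lagged model that adjusts for current negative affect, and item 6 is there to control for unpleasant events. A higher stressor rating in one arm does not by itself bias that association. Bias is possible but not shown.
- **An analysis plan may name exercise timing as a covariate.** It may, but it cannot use interval-level timing that the listed items do not collect.

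**Conclusion.** The point holds as a one-arm measurement problem of limited reach. Items 4 and 13 do not exclude assigned practice, and in the decentering arm about 11% to 15% of training beeps could report it (18% to 25% with grounding sessions). These shares assume one interval per exercise and full adherence.

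The level shift of 0.11 to 0.30 points for distancing exercises alone rests wholly on an assumed 1 to 2 point rise. The false-positive rates rest on that rise and on the assumed variances, and show where the bias can go rather than how large it will be. The exposed quantities are the arm difference in level and the change from baseline. The growth slope is exposed mainly if baseline beeps are on the time axis or practice rises in week 5. The Experiences Questionnaire power calculation is untouched. The change is worth making because it is cheap and later analysis could not fully replace it.

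**What to change.** **Preferred.** Add *apart from the programme exercises* to the since-last-beep distancing and stressor items (4, 6, 7, 12 and 13), identically in both arms.

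**Alternative.** Add one yes/no item to every beep in both arms: *Since the last beep, did you do a programme exercise?* Keep all beeps in the main randomised comparison, and pre-specify a sensitivity analysis that excludes or adjusts for exercise intervals.

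**If the app is locked.** Base that sensitivity analysis on day of week (Monday and Tuesday against Wednesday to Friday, weeks 1 to 4) and on diary-reported completion.

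In every case, state whether baseline beeps are on the time axis of the growth model.

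**Cost.** Slightly longer items, or one extra tap per beep. Excluding exercise intervals leaves at least 75% of training beeps under the one-interval assumption, but costs the lagged model more: four beeps give three same-day pairs, and dropping an interior beep removes two of them. Doing an exercise is also post-randomisation behaviour, so the sensitivity analysis is supportive only and should not replace the comparison on all beeps.
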